| Analysis                                                                   | 
Part 1 – Survey:
 
 
• Only data from those survey participants whom fit the inclusion criteria and 1) the ASG confirms are patients living with ATTR amyloidosis or 2) completed the survey but did not request financial compensation for their time and did not disclose their email address were included in the analysis (See section 3.3)
 
• Descriptive statistical analysis were performed on the closed-ended questions. In addition, thematic analysis will be conducted on the qualitative data generated by open-ended responses
 
 
Part 2 - Interviews:
                                                         |

|                                                                                                                                                                                                                                                                                                                                                                                                                                                                                                           |                                                                                                                                                                                                                 |
|-----------------------------------------------------------------------------------------------------------------------------------------------------------------------------------------------------------------------------------------------------------------------------------------------------------------------------------------------------------------------------------------------------------------------------------------------------------------------------------------------------------|-----------------------------------------------------------------------------------------------------------------------------------------------------------------------------------------------------------------|

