## 2.2 Study Rationale

To date, limited data is available pertaining to the clinical characteristics, prevalence, and burden of early ATTR amyloidosis-related disease manifestations in US patients. In particular, the early disease course of ATTRwt amyloidosis (i.e., clinical features occurring prior to heart failure) are not well characterized. The literature indicates that patients may experience neuropathy and orthopedic complications years in advance of severe cardiac dysfunction in both ATTRv and ATTRwt amyloidosis, but little has been reported on the prevalence, timing, and severity of such non-cardiac symptoms. Additionally, two clinical syndromes of ATTRv amyloidosis have been described in the medical literature: familial amyloid polyneuropathy [FAP] or familial amyloid cardiomyopathy [FAC]. This characterization is due in part to the incomplete understanding of etiology and pathogenesis in hereditary amyloidosis. More recent literature has reported that most patients with ATTRv amyloidosis manifest signs and symptoms of both polyneuropathy and cardiomyopathy over the course of their disease. Finally, due to the genetic nature of ATTRv amyloidosis, the time between early disease symptoms and diagnosis may differ in patients with a known family history compared to those who are index cases.

This observational, patient-completed online survey study with follow-on, in-depth qualitative interviews aims to achieve a better understanding of the natural history of ATTRv and ATTRwt amyloidosis leading up to diagnosis and the impact of this period of the disease on patients' lives. Relevant medical history, including signs, symptoms, diagnoses and procedures, that have been reported in the literature or reported by patients or physicians to be associated with ATTR amyloidosis were assessed. In addition, the timing of each manifestation and the physician specialty to whom these early manifestations were reported or by whom these early manifestations were managed were collected in order to gain a better understanding of the patient journey through the healthcare system during this time.

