### 3.4 Data analysis and reporting

#### 3.4.1 Analysis

##### Part 1 – Survey:

Due to the unanticipated high enrolment in the survey (>1000 responses between November 30 and December 8, 2020) and uncharacteristic patient demographics (as noted by experienced clinicians and members of the ASG) among survey participants in both hATTR amyloidosis and wtATTR amyloidosis patient groups, particularly in the last 5 days of data collection (Figure 1), it was determined that an additional data cleaning step will be required prior to data analysis to identify ‘true’ patients. A rapid acceleration in patient recruitment and notable change in the average age of participants (i.e., namely, younger participants than is typical for either hATTR or wtATTR amyloidosis) starting on the 5th day of recruitment, Friday November 4, 2020 was observed.

[figure not shown]

**Figure 1.** Day-to-day patient enrolment and mean age of participants throughout the survey recruitment period.

To strengthen internal validity, the ASG leadership confirmed each survey subject's patient status as someone living with ATTR amyloidosis before their data was included in the analysis. To accomplish this, BresMed shared the email addresses collected as part of the survey with the ASG leadership; sharing email information from the following two fields of the survey:

1. Emails provided by the participants who consented to be contacted for follow-up in depth interviews
2. Emails provided by the participants who wished to receive the \$30 Amazon gift card as compensation for their time completing the survey

The ASG leadership cross referenced these email addresses with their own patient list and flagged those emails corresponding to patients who are known to the ASG patient organization.

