Additionally, patients who completed the survey and chose not to disclose their email address, including those not to receive the compensatory Amazon gift card, will be included considered for the analysis (maximum 44 participants). It is considered reasonable by the researchers to consider these participants as likely to be patients living with ATTR amyloidosis as they did not have a financial incentive to participate in the study and were more likely to have participated for altruistic reasons. Patient demographics and disease characteristics for the subgroups ATTRwt and ATTRv amyloidosis will be summarized. Through the expert opinions of the researchers, it will be determined whether this cohort reflects the disease characteristics of subjects included in previous publications of ATTR amyloidosis. The researchers will determine whether or not to include these patients in the analysis cohort.

Additional criteria for data cleaning purposes may be considered, such as excluding:

- Responses that come from the same IP address, provided that the responses suggest that it is the same person answering twice
- Respondents that have not mentioned at least one sign/symptom, procedure or other diagnosis
- Respondents who provided inconsistent answers" (e.g. the 'faulty age' criterion, those that put ages older than their diagnosis age)

In summary, only data from participants who adhere to the inclusion criteria and are a) on the validated patient lists (i.e., confirmed by the ASG) and potentially (pending data review) b) who completed the survey but did not opt-in to receive financial compensation and did not disclose their email addresses for other reasons will be used for survey data analysis (i.e., analysis group).

The anticipated statistical or thematic analysis for each question within the survey will be shared with Alnylam for approval prior to the survey analysis. Due to the second objective being to evaluate the similarities and differences between the two conditions, the results will be separated

per condition and analyzed separately. Following this analysis, the results from the two conditions will be compared to highlight the similarities and differences.

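### Up to 44 respondents whose patient status cannot be checked are kept or dropped as a block on an undefined, data-dependent judgement that they resemble published patients, and Table 1 reports them as already included

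*Protocol*

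**What the plan says.** Section 3.4.1 (Part 1 – Survey) sets up an email check against the ASG membership list and introduces it by saying that "the ASG leadership confirmed each survey subject's patient status as someone living with ATTR amyloidosis before their data was included in the analysis". It then adds a second route. People who completed the survey without giving an email address "will be included considered for the analysis (maximum 44 participants"). The reason given is that they had no financial incentive. Their demographics and disease characteristics are to be summarised by ATTR type, and by expert opinion "it will be determined whether this cohort reflects the disease characteristics of subjects included in previous publications of ATTR amyloidosis". After that, "The researchers will determine whether or not to include these patients in the analysis cohort". The closing summary of the section lists this route as "potentially (pending data review) b) who completed the survey but did not opt-in to receive financial compensation".

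Table 1 (Analysis, Part 1) describes the same group differently: those who "completed the survey but did not request financial compensation for their time and did not disclose their email address were included in the analysis". It attaches no condition and refers to section 3.3, although the rule is in 3.4.1.

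Section 2.3 gives as the first primary objective of Part 1 a description of diagnoses, signs, symptoms and procedures between first suspected symptom and diagnosis. Section 2.2 states that "limited data is available pertaining to the clinical characteristics, prevalence, and burden of early ATTR amyloidosis-related disease manifestations in US patients".

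**The concern.** An analysis set should be fixed by criteria that do not depend on the results. Here a block of respondents who cannot be verified is summarised, compared with the literature, and kept or dropped on the outcome of that comparison. The people deciding have seen the data, and nothing fixes which characteristics count, which publications are the reference, or how close is close enough.

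The rule also has a direction. A group that looks like published patients is kept; one that looks different is dropped, even if the difference is a genuine early feature that has not yet been reported. The study is justified by how little is known about early manifestations, so this is an unhelpful direction in which to lean. Conversely, if the group contains dishonest responders, passing a loose resemblance test does not remove their influence on feature prevalence, timing or HCP results.

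Finally, a reader of the current text cannot tell whether the group is in the analysis, because Table 1 and section 3.4.1 give it different statuses.

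**Working it through.** **Text comparison.**

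| Place | Status of the no-email group |
|---|---|
| Table 1 | included, past tense, unconditional |
| Section 3.4.1, paragraph on the group | to be decided by the researchers after the summary and the comparison with publications |
| Section 3.4.1, closing summary | potentially included, pending review |
| Section 3.4.1, sentence introducing the email check | every subject confirmed by the ASG |

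Row 1 conflicts with rows 2 and 3. Row 4 cannot apply literally to people with no email, because the check is an email match.

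**Size.** The plan's own figure, 44, is a count from the collected data, so there is no formula to reproduce. It is 44/1,022 = 4.3% of the clicks, but the relevant denominator is the analysis set.

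Inputs:
- n = 44, the maximum in section 3.4.1.
- V = number of ASG-confirmed respondents. Not stated, so assumed to be 60, 100 or 200. The value 60 equals the minimum enrolment target in section 2.4.3; it is not a verified count.
- f = fraction of the 44 who are not patients, assumed 0.25 to 0.75.
- g = difference in the prevalence of a feature between those non-patients and true patients, assumed 20 to 40 percentage points.

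Share of the analysis set = 44/(44 + V):
- V = 60: 44/104 = 42.3%
- V = 100: 44/144 = 30.6%
- V = 200: 44/244 = 18.0%

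Shift in pooled prevalence = share × f × g:
- V = 60: low 0.423 × 0.25 × 20 = 2.1 points; high 0.423 × 0.75 × 40 = 12.7 points
- V = 200: low 0.180 × 0.25 × 20 = 0.9 points; high 0.180 × 0.75 × 40 = 5.4 points

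These are pooled over both ATTR types. Section 3.4.1 analyses the types separately, so the shift within one type could be larger if the 44 fall unevenly between them.

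**The case against.** The best defence is that this is a disclosed plausibility check. The protocol describes the procedure before the decision is taken, the decision is on the block and not person by person, ASG-confirmed respondents are never selected this way, and Part 1 is descriptive with no stated hypothesis test. All of that is true and limits the reach of the problem. It does not supply a criterion.

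A reader might infer more than the text supports in four respects.

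- *That the rule selects directly on the study outcomes.* Section 3.4.1 does not define disease characteristics. They could mean general features such as phenotype, on which sections 2.1 and 2.2 do cite published work; the scarcity described in section 2.2 concerns early manifestations in US patients. Overlap with the pre-diagnosis outcomes is likely, since nothing excludes it, but it is not stated. It would also go too far to say that the survey could not count as new evidence.
- *That three statements about the group are irreconcilable.* The sentence on confirming each subject introduces the email check, and the no-email route is then presented as an addition to it. It is loose wording. The conflict that stands is between Table 1 and section 3.4.1.
- *That the plan's warning signs of dishonest response are not applied to this group.* Those signs were younger age and accelerated enrolment. The demographic summary would ordinarily show age, and section 3.4.1 lists further possible exclusions (repeated IP address, no reported manifestation, inconsistent ages). Only enrolment date is left unused.
- *That restricting the group to enrolment before day 5 would be a clean remedy.* That cut-off was itself observed in the collected data, and it would discard genuine later respondents.

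The size also depends on assumptions. The lack of financial incentive argues for a non-patient fraction towards the low end, and 44 is a maximum.

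**Conclusion.** The point holds in a bounded form. Section 3.4.1 lets the composition of the analysis set turn on an unspecified judgement, made after seeing the data, about whether an unverifiable group resembles published patients. In a study whose primary objective is to describe disease presentation, that makes the set depend on data likely to overlap with the outcomes and favours agreement with the literature. The bias is confined to this group of at most 44.

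Whether it is material depends on the unstated number of ASG-confirmed respondents. Across the assumed range the group would be 18% to 42% of the set, and one yes/no decision could move a pooled prevalence by anything from about 1 to about 13 points. The verified count, the non-patient fraction and the prevalence gap are all assumptions. The undefined rule and the mismatch between Table 1 and section 3.4.1 stand without them.

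**What to change.** 1. In section 3.4.1, define the primary Part 1 analysis set as respondents who meet the inclusion criteria and are confirmed by the ASG.
2. Delete resemblance to earlier publications as a condition for inclusion. The comparison may stay as description.
3. Report the no-email group in a separate column and in one pooled sensitivity analysis, regardless of how it looks. Its enrolment dates may be tabulated descriptively but should not be a filter for the primary set.
4. Give the group the same status in Table 1 and section 3.4.1, correct the cross-reference in Table 1, and limit the sentence on ASG confirmation to respondents who gave an email address.

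The cost is wording, one extra column and one extra set of tables; no new data are needed. If the group has already been included, results with and without it can still be produced. The primary set may shrink by up to 44. It may also under-represent genuine patients unknown to the ASG, for example those reached through HCPs (section 2.4.2). The pooled sensitivity analysis addresses this for those who gave no email.

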## **Part 2 – Interviews:**

In qualitative research, thematic analysis is frequently used to recognise patterns in the collected data and based on that, test hypotheses and/or form new ideas. These themes can either come from previous research and theories (deductive) or can be newly identified through investigating what themes emerge from the data (inductive), or a combination of both.

For this research, thematic analysis will be used to identify recurring themes, using both inductive and deductive coding methods. A coding framework (i.e., a framework with initially identified themes that will be used for coding the data) will be developed and implemented.

The stages involved in thematic analysis can be broadly divided as follows:

1. Familiarisation with data (becoming thoroughly immersed in the material collected)
2. Developing a thematic framework (identifying key issues from data)
3. Coding the data (labelling key issues that emerge across a set of data)
4. Devising a series of thematic charts (allowing the full pattern across a set of data to be explored and reviewed)
5. Mapping and interpreting data (looking for associations, providing explanations and highlighting key characteristics and ideas)

Data will be managed and analysed using QSR NVivo software, which is specifically designed for the analysis of qualitative data.

### **3.4.2 Reporting**

The final anonymized and aggregated patient results from the survey will be reported within a PowerPoint presentation. This will highlight the key findings of the survey for Alnylam Pharmaceuticals, the ASG, or clinical experts to consider.

A summary report from the qualitative interviews will be generated in a Word document, including a thematic summary of key points raised by patients related to each research objective as well as supporting, de-identified patient quotes.

Any external publication or disclosure to the medical community, health authorities, or patient organizations, if any, will be limited to the anonymized findings of this research.

## **3.5 Confidentiality and data protection**

### **3.5.1 Confidentiality and data protection**

Identifiable data linking the participants to their survey or interview responses will not be shared with Alnylam Pharmaceuticals, the ASG, or clinical experts and will only be accessible to the BresMed team. In summary, participant data will be stored on a secure server and in a password-protected location. BresMed will only share participant email addresses with the ASG for analysis purposes due to the unexpectedly high response rate (please see section 3.3.1). No other data (physical or soft copies) or personally identifiable subject information will be shared outside the BresMed office or folder on the server. Only the research team within BresMed will have access to this folder. Once the project is completed, the data will be stored on a secured file and archived for 3 years. BresMed is trained in upholding General Data Protection Regulation (GDPR) and will not store data on flash drives or computers other than those specific for work. When possible, data will not be stored on individual computers, and access to those computers (that access the server) will be locked in offices overnight. Encrypted and multifactor authentication processes have been put in place that will prevent access to the server to anyone other than BresMed employees.

In detail, to protect the participants' confidentiality, several safeguards will be implemented:

- If a participant decides not to take part in the research, personal identifiable information will only be held where needed for compliance with law. No further data will be retained
- If requested by the participant, any personal identifiable information held by BresMed will be shared with them
- It will be made clear that a participant can opt-out of the survey or have their data excluded from analysis and results by emailing a researcher to request withdrawal of their data from the study
- Only aggregated data will be published. This data cannot be revised should a participant withdraw consent after publication
- During the process of verification of participants' patient status, all personal information (i.e., patient emails) will be shared directly between BresMed and the ASG. Alnylam and the HCP clinical experts will be blinded to all personal data and will not be involved in this additional data cleaning procedure
- All transcripts and publishable quotes will be redacted of any personal identifiable data and not be shared with Alnylam

### 3.5.2 Adverse event reporting

BresMed must comply with all Adverse Event and Product Complaint reporting obligations under applicable laws in the United States and send copies of all reports (including but not limited to interim study reports, final study reports, etc.) submitted to any health authority or regulatory agency regarding an Alnylam product in parallel to Alnylam via Email:

**[contact]** or [contact]**.

Additionally, BresMed must report all Adverse Events (AEs) (as defined below) and/or Other Safety Information (as defined below) concerning Alnylam's products to Alnylam Global Patient Safety and Risk Management within 24 hours of first knowledge by BresMed via Email:

**[contact]** or [contact]**.

BresMed must report all Product Complaints (PCs) (as defined below) via Email:

**[contact]**

BresMed shall ensure that any personal information collected about individuals complies with applicable privacy and data protection laws and regulations.

Definitions:

**Adverse Event (AE):** Any untoward medical occurrence in a patient administered an Alnylam marketed product and which does not necessarily have a causal relationship with this treatment. An adverse event can therefore be any unfavourable and unintended sign (for example, an abnormal lab finding) symptom, or disease temporally associated with the use of an Alnylam marketed product, whether or not considered related to this Alnylam marketed product.

**Other Safety Information:** Other Safety Information means circumstances where a report does not include an AE per se, but nevertheless needs to be reported to Alnylam. These circumstances include:

- Use of a product during pregnancy or breastfeeding
- Overdose
- Abuse
- Misuse
- Medication error
- Occupational exposure
- Lack of therapeutic efficacy
- Off-label use
- Suspected transmission via a medicinal product of an infectious agent
- Suspected or confirmed counterfeit/falsified medicinal product

**Product Complaint (PC):** Any written, electronic, or oral communication that alleges deficiencies related to the identity, quality, durability, reliability, safety, effectiveness, or performance of a medicinal product, medical device, or combination product after it is released for distribution. Product

complaints are typically non-medical in nature; however, it is possible that complaints could be associated with an adverse event.

